### Clinical outcome assessments

The primary outcome will be the mean difference in the changes in office SBP from baseline to 4 weeks between the two groups. SBP will be measured using a unified automated monitor (HEM-7136, Omron, Kyoto, Japan), and follow the WHO STEPS protocol for the procedure. The arm with higher blood pressure in the patient at baseline will be selected as the measurement arm throughout the study. Before each measurement of the patient’s blood pressure, the patient will be asked to sit and rest for 5 minutes with the upper arm at the level of the heart. Then, the blood pressure measurement will record three values in succession at 5-minute intervals, and the final blood pressure being the average of the last two times [36,37].

Secondary outcomes will include differences in the changes in office DBP between the two groups; the proportion of patients with well-controlled blood pressure (office blood pressure <140/90 mm Hg); and differences in the changes in the quality of life assessed using 12-item Short Form Health Survey (SF-12) [38]; physical activity assessed using International Physical Activity Questionnaire (IPAQ) [39]; quality of sleep assessed using Pittsburgh Sleep Quality Index (PSQI) [40]; the severity of current anxiety symptoms assessed using State-Trait Anxiety Scale State Anxiety Subscale (STAI-S) [41].

Safety outcomes will be any acupuncture-related adverse events (pain, panic, and subcutaneous hematoma) at weeks 2, 4, and 8 in both groups. All patients will be asked to guess which treatment they have received at week 2 and week 4 as blinding assessments. All patients’ physical condition, cognitive function, or other eligibility will be monitored during the trial.

### MRI data acquisition

The MRI scan will be performed with a 3.0 Tesla scanner (Siemens, Germany) in the Dongzhimen Hospital Affiliated to the Beijing University of Chinese Medicine. Patients will undergo fMRI scans at baseline and the end of the intervention. In addition, the HCs will undergo only one scan. Before scanning, they will be required to wear earplugs and remove all magnetic and metal items. In the meantime, they will be asked to maintain a comfortable supine position and reduce head movements.

Echo planar imaging (EPI) sequence is used for resting-state fMRI scanning: whole brain, repetition time (TR) = 2000 ms, echo time (TE) = 30 ms, field of view (FOV) = 224 mm × 224 mm, flip angle (FA) = 90°, slice thickness = 3.5 mm, axial slices = 32, size of voxel = 3.5 mm × 3.5 mm × 3.5 mm, in-plane resolution = 64 × 64, and volumes = 240.

### Photoplethysmography assessment

Pulse oximetry collects pulse waves from fingertips by PPG measurements for PRV analysis. Image-based PPG that could measure skin blood flow fluctuations from raw digital camera images and allow us to extract pulse wave signals from video. In this study, we will use a finger-clip pulse oximeter (CONTCS, CMS60E) to collect the pulse signal for 2 minutes. In addition, we will use a smartphone camera (iPhone 14 Pro) to record a video (40 seconds) of the acupuncture points in the arm at a speed of 30 frames per second with a resolution of 1920 *1080 pixels. All patients will be evaluated before and at the end of treatment, respectively. Autonomic activity could also be reflected by analyzing the morphology of signal waves. In this study, we will mainly analyze the general time domain parameters and frequency domain parameters.

### Data management and quality control

Clinical data for all patients will be collected using a case report form (CRF). All researchers will be trained in questionnaire evaluation and data management. The data will be entered into an Excel spreadsheet independently by the two researchers on time, and then the data will be checked for completeness and accuracy. When there are discrepancies, refer to the original CRF to correct the data. All paper and electronic documents in this study will be reasonably kept. If readers and reviewers have any questions regarding our published data, they can contact the corresponding author to request the original data. In addition, we will protect patients’ private information, such as names and phone numbers. The patients will be scanned by a professional imaging technician on the same MRI scanner and the quality of the imaging data will be checked after each scan. Finally, we will establish a trial steering committee composed of the primary investigators ([name], [name] and WX) and statistician to monitor the progress and data quality of this study every 3 months.

### Statistical analysis

#### Clinical data analysis.

The clinical data will be analyzed by an independent statistician using IBM SPSS V.20.0 software, and the *P* values < 0.05 will be considered statistically significant. For those conforming to a normal distribution, the data will be described utilizing the mean (standard deviation), otherwise, the median (quartile spacing) will be used. The categorical data will be described as percentages (%). We will use the independent sample t test to compare the effect of EA vs. SE on blood pressure from baseline to week 4. For the other outcomes, if data conforms to a normal distribution, it will undergo t-test analysis. Conversely, if it does not conform to the normal distribution, it will be analyzed by nonparametric test. Categorical data will be analyzed via the χ^2^ test or Fisher’s exact test. All cases of randomized patients will be undertaken on the intention-to-treat analysis, and missing values will be filled in using multiple imputations. To evaluate the stability of results, we will conduct a sensitivity analysis with the last observation values. A per-protocol analysis will include the patients who complete at least 80% of the study.

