### Sample size

The sample size is calculated based on the decrease in SBP from baseline to week 4. According to the prior research [27–30], we assume that the mean SBP change value at week 4 in the EA group reaches 5 mm Hg with a standard deviation of 5 mm Hg, and in the SE group, the mean SBP change value reaches 1 mm Hg with a standard deviation of 5 mm Hg. The sample size of 26 patients in each group was calculated to provide 80% power, with a two-tailed α level of 0.05, using PASS 2021 software. This requires 33 patients per group allowing for 20% dropout.

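### The only stated missing-data sensitivity analysis is last observation carried forward, which does not systematically test departures from missing at random and can bias the difference either way

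*Protocol article*

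**What the plan says.** The Clinical data analysis section of the protocol article puts all randomized patients into an intention-to-treat analysis in which "missing values will be filled in using multiple imputations". The primary comparison is a t test: "We will use the independent sample t test to compare the effect of EA vs. SE on blood pressure from baseline to week 4". One check on the handling of missing data follows: "To evaluate the stability of results, we will conduct a sensitivity analysis with the last observation values". The same section also lists a per-protocol analysis: "A per-protocol analysis will include the patients who complete at least 80% of the study". That changes who is analysed and leaves the assumption about the missing values untouched.

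The Sample size section shows how much missing data is allowed for: "This requires 33 patients per group allowing for 20% dropout". According to the abstract's design paragraph, outcomes are measured at baseline and at weeks 2, 4 and 8. The only values that can be carried forward to week 4 are therefore those from baseline and week 2.

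**The concern.** Multiple imputation, as usually implemented, assumes that data are missing at random given what was observed. A check on the stability of its result should vary that assumption and show how far it can fail before the conclusion changes. An example of failure is patients leaving because their pressure did not fall.

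LOCF does not do this. A patient lost before week 2 is given a change of exactly zero. A patient lost later is given the value from halfway through the treatment course. Both are then analysed as if measured at week 4. This is one fixed alternative assumption, and an implausible one, applied to both arms.

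The choice matters here because the dropout allowance is large for a small trial. Dropout could also differ between arms. The Informed consent and participant safety section lets patients withdraw if they cannot tolerate adverse effects, and the Interventions section describes manipulated, electrically stimulated needling in one arm against shallow needling without current in the other. The only stated support for the robustness of the main result would be a method with biases of its own.

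**Working it through.** **Inputs from the Sample size section.** In the electroacupuncture arm (EA), "the mean SBP change value at week 4 in the EA group reaches 5 mm Hg with a standard deviation of 5 mm Hg". In the sham arm (SE), "the mean SBP change value reaches 1 mm Hg with a standard deviation of 5 mm Hg". The planned difference is 5 − 1 = 4 mm Hg, with 80% power, two-sided 5% level and 1:1 allocation.

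**Reproducing the plan's figure.** The t-test solution is 25.52, so 26 per group, with power 80.7%. Allowing for dropout, 26/0.8 = 32.5, so 33. The plan's figures reproduce. Patients per arm who may lack the week-4 value: 33 − 26 = 7.

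**Assumptions not in the document.** Dropout fraction *d* per arm, completely at random; share *e* of dropouts lost before week 2; share *f* of the week-4 mean change already present at week 2. For the simulation (20,000 trials per scenario, 33 per arm), the correlation between week-2 and week-4 change is 0.6.

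**Balanced dropout.** The expected LOCF mean in an arm with true mean change *m* is *m* × [(1 − *d*) + *d*(1 − *e*)*f*]. With equal *d*, *e* and *f* in both arms, the expected difference is 4 × [(1 − *d*) + *d*(1 − *e*)*f*]. With *d* = 0.20:

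| Lost before week 2 (*e*) | Effect at week 2 (*f*) | Calculation | LOCF difference | Simulated difference |
|---|---|---|---|---|
| all | any | 4 × 0.80 | 3.2 | 3.20–3.21 |
| half | half | 4 × 0.85 | 3.4 | 3.41 |
| none | half | 4 × 0.90 | 3.6 | 3.61 |
| none | full | 4 × 1.00 | 4.0 | 4.00 |
| none | 125% | 4 × 1.05 | 4.2 | 4.21 |

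The observed-case difference in these simulations is 4.0 throughout, because dropout was made completely at random. The departures from 4.0 come from LOCF itself, so disagreement with multiple imputation need not signal informative dropout.

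**Agreement can also mislead.** Suppose all dropouts leave after week 2 with the full effect present (*f* = 1), and their pressure then returns to baseline by week 4. The true difference over all randomized patients is 0.8 × 4 = 3.2. LOCF gives 4.0. Multiple imputation from completers with the same week-2 means also gives about 4.0. The two agree, and both miss the departure.

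**Unequal dropout, no true effect.** Assume a 5 mm Hg fall in both arms, *e* = 0.5 and *f* = 0.5, with 10% dropout in EA and 30% in SE.

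- EA: 5 × (0.90 + 0.10 × 0.5 × 0.5) = 5 × 0.925 = 4.625
- SE: 5 × (0.70 + 0.30 × 0.5 × 0.5) = 5 × 0.775 = 3.875
- Difference: 0.75. With the dropout rates exchanged it is −0.75.

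The simulation gives +0.76 and −0.74, with type I error of 9.8% and 9.3%. The spurious difference is 0.15 times the common fall, so with a common fall of 1 mm Hg it would be only 0.15 mm Hg.

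**Precision.** In the balanced scenarios the mean LOCF standard error is about 1.15 to 1.28, against about 1.37 for observed cases, because carried values count as week-4 measurements. In the half/half scenario the LOCF standard error (1.20) equals the estimator's own sampling SD (1.20).

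**The case against.** The primary analysis is already multiple imputation in all randomized patients, so the main estimate does not depend on LOCF. Nor is LOCF wholly uninformative. For an EA patient lost before week 2 it assigns zero change, which is harsher than the 1 mm Hg fall assumed for the sham arm. It is thus a crude departure from missing at random. The 20% is a planning allowance, and the dropout pattern is assumed. In the half/half scenario the test statistic barely moves: 3.4/[5 × √(2/33)] = 3.4/1.23 = 2.76 under LOCF, against 4/[5 × √(2/26)] = 4/1.39 = 2.88 for 26 observed per arm. These points stand, and they limit the finding to the quality of the robustness check.

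A reader might infer more than the document supports:

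- **That LOCF attenuates the effect.** This holds when the effect is still building or dropouts leave early. It is not general: the estimate is unbiased or slightly inflated in other scenarios, and unequal dropout can push it either way.
- **That LOCF understates its standard error.** As a property of the LOCF estimator this is wrong, since its standard error matches its sampling SD. What is true is that carried values are counted as week-4 observations.
- **That imputation cannot be combined with the tests for secondary outcomes**, where for non-normal data "it will be analyzed by nonparametric test". This is a separate matter. Pooling rules are commonly left to the statistical analysis plan, and the article rules none out.

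A fuller analysis plan may add other analyses. LOCF is nevertheless the check that the article itself states, so this is a point about stated text and not about an omission.

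**Conclusion.** The concern holds in limited form. The one stated missing-data check swaps missing at random for a single fixed and implausible assumption, so it does not show how large a departure the result could withstand. Agreement with the primary analysis would be weak reassurance, and disagreement could be LOCF's own bias.

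The 3.2 to 4.2 mm Hg range rests on balanced 20% dropout completely at random and on assumed values for dropout timing and the week-2 effect. The 0.75 mm Hg figure rests on 10% versus 30% dropout and a common 5 mm Hg fall. None of these patterns is in the document. They show what LOCF can do; they do not predict this trial's result. The documents support neither a fixed direction of bias nor a claim that the primary estimate is invalid.

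**What to change.** In the Clinical data analysis section, replace LOCF as the sensitivity analysis, or demote it to a supplementary analysis. Make the stated check a delta-adjusted (tipping-point) analysis on the same multiple imputations: worsen the imputed week-4 systolic pressure in the EA arm in fixed steps until the conclusion changes, and report the step at which that happens. With 7 of 33 EA values imputed, each 1 mm Hg of adjustment moves the difference by 7/33 = 0.21 mm Hg, so the result is easy to read. Imputing EA dropouts from the SE arm (reference-based) is an optional addition.

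The cost is a revised sentence and modest extra programming. No new data are needed, and the change should be fixed before unblinding.

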#### Neuroimaging data analysis.

The fMRI data will be analyzed using the Data Processing Assistant and Resting-State fMRI (DPARSF) and SPM toolbox based on MATLAB software (Mathworks, Inc., Natick, MA, USA). The preprocessing will include DICOM format conversion, removing the first 10 volumes, slice timing, head motion correction, spatial standardization (resampled to 3 mm × 3 mm × 3 mm), removing linear trend, low-frequency filtering (0.01–0.08 Hz), and regression removal of covariates (head motion parameters, white matter signal, grey matter signal or/and global signal), spatial smoothing with 6 mm FWHM Gaussian kernel. Participants with more than 3 mm of displacement in x, y, or z or 3 degrees of angular head motion will be excluded in further analyses. After data preprocessing, we will compare the brain region changes between EH patients and HCs. Then the amplitude of low-frequency fluctuation (ALFF), regional homogeneity (ReHo), or functional connectivity (FC) analysis will be performed to investigate the brain responses significantly associated with the antihypertensive effects of acupuncture. Gaussian Random Field (GRF) correction will be applied for multiple comparison correction. These indicators are the most commonly used in current fMRI analysis. Previous studies found that there are abnormal ReHo values of insula and enhanced FCs between brain networks in the hypertension patients [42,43]. Pearson or Spearman correlation analysis will be used to test the correlation between fMRI data and clinical measurements. The False Discovery Rate (‌FDR) correction is applied to correct the potential type I errors caused by multiple testing. Then, we will further conduct multiple regression and support vector regression (SVR) analyses to explore the predictive factors affecting the therapeutic effect of acupuncture for blood pressure.

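### As written, ReHo is computed on data already smoothed at 6 mm, which inflates local concordance and compresses real differences; the filter-before-regression order also needs a condition stated

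*Protocol article*

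**What the plan says.** The Neuroimaging data analysis section of the protocol article lists the preprocessing from format conversion through normalisation to 3 mm voxels. It continues with "removing linear trend, low-frequency filtering (0.01–0.08 Hz), and regression removal of covariates" and closes with "spatial smoothing with 6 mm FWHM Gaussian kernel". The covariates to be regressed out are "head motion parameters, white matter signal, grey matter signal or/and global signal".

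The analyses follow: "After data preprocessing, we will compare the brain region changes between EH patients and HCs". The next step is given as: "Then the amplitude of low-frequency fluctuation (ALFF), regional homogeneity (ReHo), or functional connectivity (FC) analysis will be performed".

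Nothing in the article exempts ReHo from the smoothing, and nothing says whether the regressors pass through the same band-pass filter as the data. The MRI data acquisition section gives "repetition time (TR) = 2000 ms" and 240 volumes, of which the first 10 are dropped.

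**The concern.** ReHo is a concordance coefficient (Kendall's W) between the time series of a voxel and those of its neighbours. Smoothing replaces each series with a weighted average of the same neighbours. If it comes first, part of the measured agreement is made by the kernel, and voxels that really differ in local synchrony end up close together near the ceiling.

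The section cites earlier ReHo findings in the insula as part of its rationale. The fMRI measures also go on to the correlations with clinical measurements and to the regression and support vector models. A blunted ReHo measure would carry through all of these.

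A second ordering issue is attached. Once a series has been filtered to 0.01-0.08 Hz, regressing it on covariates that still contain other frequencies can put those frequencies back into the residuals.

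**Working it through.** The imaging plan states no figure to reproduce, so the check starts from its parameters.

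**Inputs from the article.** 6 mm FWHM; 3 mm voxels; 0.01-0.08 Hz; TR 2 s; 240 - 10 = 230 volumes.

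**Assumptions.** A 27-voxel (3×3×3) neighbourhood; where stated, 4 mm intrinsic smoothness; the shared-signal fractions; the number and type of regressors.

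**1. Independent noise, by formula.** W is approximately the mean of the 27×27 correlation matrix, diagonal included.
- Unsmoothed: 1/27 = 0.037.
- The kernel is 6/3 = 2 voxels FWHM, so σ = 2/2.355 = 0.849 voxels. Smoothed white noise has correlation exp(-d²/4σ²) at a distance of d voxels: 0.707 at d = 1 and 0.25 at d = 2.
- Along one axis of three voxels, the nine ordered pairs average (3×1 + 4×0.707 + 2×0.25)/9 = 0.703. The kernel is separable, so W ≈ 0.703³ = 0.348.
- Simulations using ranks gave 0.037-0.038 unsmoothed and 0.33-0.34 smoothed, about ninefold, in agreement with the formula.

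**2. Noise with intrinsic smoothness.** With 4 mm assumed, the simulations gave 0.13 without the planned smoothing and 0.41-0.43 with it, about 3.2- to 3.3-fold. This is nearer to real data than step 1, because acquired 3.5 mm voxels resampled to 3 mm are not independent.

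**3. Real shared signal.** Let a fraction ρ of each voxel's variance be common to the whole region.
- Unsmoothed: W = (1 + 26ρ)/27. For ρ = 0.1 this is 3.6/27 = 0.13; for ρ = 0.6 it is 16.6/27 = 0.61.
- Smoothing leaves the common signal alone and multiplies the noise variance by [1/(2σ√π)]³ = 0.332³ = 0.037. The shared fraction becomes ρ' = ρ/(ρ + 0.037(1-ρ)), and W ≈ ρ' + (1-ρ')×0.348.
- ρ = 0.1: ρ' = 0.1/0.1333 = 0.750, so W ≈ 0.84. ρ = 0.6: ρ' = 0.6/0.6148 = 0.976, so W ≈ 0.98.
- Simulation gave 0.12-0.13 to 0.61 unsmoothed and 0.82-0.83 to 0.98 smoothed. By formula the width falls from 0.615 - 0.133 = 0.48 to 0.984 - 0.837 = 0.15.

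**4. Effect on a group comparison.** The spread between subjects is compressed as well, so the loss in standardised terms is smaller. A single-run simulation compared ReHo followed by smoothing with smoothing followed by ReHo (60 per group, 4 mm intrinsic smoothness, between-subject SD of the shared fraction 0.1, all assumed):

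| Shared fraction | Cohen's d, ReHo first | Cohen's d, smoothing first |
|---|---|---|
| 0.4 v 0.5 | 0.61 | 0.51 |
| 0.2 v 0.3 | 0.94 | 0.82 |

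In the first row the raw difference in W fell from 0.055 to 0.015. These are indicative figures only.

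**5. Filtering and regression.** The share of residual variance outside 0.01-0.08 Hz was:

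| Order | Out-of-band share |
|---|---|
| Regress, then filter | about 0% |
| Filter, then regress on identically filtered covariates | about 0% |
| Filter, then regress on unfiltered covariates, 8-9 regressors | 11-18% |
| The same, 26 regressors | 23-28% |

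A separate white-noise check with unfiltered covariates gave only 2-8%, so the size depends heavily on the assumptions.

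**The case against.** The strongest reply is that the order is inferred. The article says what preprocessing will include, not that the steps run in that sequence. The paragraph is loose elsewhere too: the patient-control comparison is placed before the metrics it would need, and the head-motion exclusion comes after smoothing although it depends on an earlier step. A condensed article may also leave pipeline detail to a fuller document.

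This has some weight, but it does not remove the point. The steps up to normalisation stand in execution order, ReHo is placed after preprocessing, and nothing exempts it. The article therefore states an order that is wrong for a measure it names. If the actual pipeline differs, the text misdescribes it.

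Other parts of the reply stand in full:
- The ninefold rise assumes spatially independent noise and is a worst case.
- The same kernel is applied to both arms, both scans and the healthy controls. A reader might infer a spurious treatment effect from the inflation. The documents do not support that: a common shift in level does not by itself create a difference.
- A reader might also infer that removed noise is certainly reintroduced. That requires unfiltered regressors, and the article is silent. Tissue or global signals extracted after filtering would already be in band; motion parameters would not be unless filtered deliberately.
- ReHo is one of three metrics joined by an or ("regional homogeneity (ReHo), or functional connectivity (FC) analysis will be performed"), in an objective the Background calls preliminary. No imaging measure appears among the outcomes in Clinical outcome assessments.

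**Conclusion.** The point holds in a limited form. Followed as written, the plan measures local concordance after averaging the voxels concerned. This raises W mechanically and compresses real differences to roughly a third of their width (0.48 to 0.15 in the worked example). The consequence is some loss of sensitivity and spatial specificity in an exploratory analysis. The indicative loss in standardised effect is modest, at about 13-16% (0.82/0.94 = 0.87; 0.51/0.61 = 0.84).

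These sizes rest on a 27-voxel neighbourhood, on the assumed intrinsic smoothness, and on shared signal that is uniform across the kernel. The filtering point is secondary and conditional: between about 2% and 28% of residual variance out of band if the regressors are unfiltered, and about none if they are filtered identically.

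The plan should be corrected, but this is not a fault that undermines the trial. The sample size, the systolic blood pressure outcome and the clinical analyses are unaffected.

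**What to change.** Add two statements to the Neuroimaging data analysis section:

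1. ReHo is computed on unsmoothed, normalised data, and the resulting ReHo maps are then smoothed at 6 mm FWHM. Smoothing before ALFF and FC stays as planned.
2. Covariates are regressed out before band-pass filtering or, if filtering comes first, every regressor, including the motion parameters, is filtered identically.

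Giving the ReHo neighbourhood size in the same place would make the measure reproducible. The cost is a few lines of text and a re-ordering of processing steps before the images are analysed, with no new scans or participants. If the pipeline already works this way, only the description changes.

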**Study design and methods:**

his is an 8-week, parallel-grouped, randomized clinical trial. A total of 66 patients diagnosed with EH are randomly assigned (1:1) to receive either the electroacupuncture or sham electroacupuncture treatment 3 sessions per week for 4 weeks. The primary outcome is the mean systolic blood pressure change at week 4 from the baseline measurement. The independent sample t-test will be used to compare the differences between two groups. The secondary outcomes include the change in mean diastolic blood pressure, the proportion of patients with controlled blood pressure (< 140/90 mm Hg), and quality of life. The outcome variables are measured at baseline, week 2, week 4 and week 8. Functional magnetic resonance imaging scans, pulse rate variability acquisition, and image-based photoplethysmography recording are performed at baseline and the end of the intervention period to explore acupuncture-related neuroplasticity changes. Correlation analyses are performed to investigate the relationships between the neural changes and clinical symptoms. Adverse events during the trial are monitored.

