It is suggested that the imbalance in the autonomic nervous system with enhanced sympathetic activity is one of the pathogenesis of hypertension, which is controlled by key brain nuclei and neural circuits in the central nervous system [18,19]. Studies have found that the regulation of autonomic parameters is associated with lower blood pressure in hypertensive people [20]. However, whether acupuncture regulates blood pressure by affecting the autonomic nervous system and the central mechanism is unclear. Functional magnetic resonance imaging (fMRI) could observe the functional activity changes of the brain, and in recent years, it has been used to explore the central mechanism of acupuncture effect [21]. In addition, contact and image-based photoplethysmography (PPG) could detect important body physiological and pathological information (e.g., pulse rate variability [PRV] and blood pressure) from the transformed pulse wave signal to detect autonomic neuromodulation, and they also could be used as the non-invasive quantitative indicators of sympathetic and parasympathetic tone and functional status in clinical practice [22–24]. Based on the above, we aims to perform a randomized controlled clinical trial in patients with essential hypertension (EH) to evaluate the efficacy and safety of electroacupuncture (EA) vs. sham electroacupuncture (SE). The second objective is to preliminarily assess the underlying central integration mechanism of acupuncture on reducing blood pressure by combining neuroimaging and neural detection techniques.

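### The brain–clinical correlations have no arm term and no stated analysis set: pooled, they inflate false positives; in the EA arm alone, they lose power and the sham comparison

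*Protocol article*

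**What the plan says.** The Background gives the objective served here: "The second objective is to preliminarily assess the underlying central integration mechanism of acupuncture on reducing blood pressure". The MRI data acquisition section has both randomised arms scanned twice: "Patients will undergo fMRI scans at baseline and the end of the intervention".

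The Neuroimaging data analysis section plans ALFF, ReHo or functional connectivity analyses "to investigate the brain responses significantly associated with the antihypertensive effects of acupuncture". It then names the test: "Pearson or Spearman correlation analysis will be used to test the correlation between fMRI data and clinical measurements". The Abstract describes the same step as relating changes: "Correlation analyses are performed to investigate the relationships between the neural changes and clinical symptoms". For multiplicity, an FDR "correction is applied to correct the potential type I errors caused by multiple testing". Multiple regression and support vector regression follow, as "analyses to explore the predictive factors affecting the therapeutic effect of acupuncture for blood pressure", with no covariates listed.

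None of these places says whether the correlations use both arms together, each arm separately, or the EA arm only. None mentions arm adjustment or a partial correlation.

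The Sample size section assumes a mean systolic change of 5 mm Hg under EA, while "in the SE group, the mean SBP change value reaches 1 mm Hg", with an SD of 5 mm Hg in each arm.

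**The concern.** A Pearson or Spearman coefficient between two variables has no place for a third. In a two-arm trial, arm can be a common cause of both variables. If EA lowers systolic pressure and also moves a brain measure, each arm forms its own cloud of points. The offset between the clouds produces a correlation, although patients within an arm show no tendency for larger brain changes to go with larger pressure changes. The pooled test then largely restates the two arm differences, and it could be read as evidence that the brain change carries the pressure effect.

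Restricting the test to the EA arm avoids this fault and creates others. Half the patients drop out of the analysis. The result also cannot show whether the same link appears under sham, which is the comparison the control arm makes possible.

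At stake is the interpretation of the second, preliminary objective.

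**Working it through.** **The protocol's own figure.** Difference 5 − 1 = 4 mm Hg, SD 5, so the standardised effect is 4/5 = 0.8. With the exact t-test at two-sided 0.05, power is 79.1% at 25 per arm and 80.7% at 26, so 26 per arm is reproduced. Allowing for 20% dropout, 26/0.8 = 32.5, which rounds up to 33. The 0.8 SD input below is therefore the plan's own, and 26 and 33 per arm are used as the two sample sizes.

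**Inputs for the correlation.**
- Arm effect on systolic change: d1 = 0.8 SD (Sample size section).
- Arm effect on the brain measure: d2. The documents give no figure, so it is an assumption, ranged from 0.3 to 1.5 SD.
- Correlation within each arm: zero, so a significant result is a false positive for a within-arm link.
- Allocation 1:1; test level 0.05 two-sided for one test, before FDR.

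**Correlation induced by pooling.** With zero within-arm correlation,

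r = (d1·d2/4) / √[(1 + d1²/4)(1 + d2²/4)]

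- d2 = 0.3: 0.06/√(1.16 × 1.0225) = 0.055
- d2 = 0.8: 0.16/√(1.16 × 1.16) = 0.138
- d2 = 1.5: 0.30/√(1.16 × 1.5625) = 0.223

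**How often the pooled Pearson test is significant** (simulation, 20,000 trials per setting):

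| Assumed brain effect (SD) | 26 per arm | 33 per arm |
|---|---|---|
| 0 | 5.1% | 4.9% |
| 0.3 | 6.6% | 7.2% |
| 0.5 | 9.7% | 11.2% |
| 0.8 | 15.7% | 19.9% |
| 1.0 | 22.0% | 27.2% |
| 1.2 | 27.5% | 34.2% |
| 1.5 | about 37% | about 44% |

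Spearman, run for effects up to 1.2 SD, stays within about 1 percentage point of these figures. Removing the arm means first (the partial correlation) gives about 5% in every setting. So does a correlation inside one arm, in the settings where it was run (0 to 1.2 SD). At 1.5 SD with 33 per arm, repeat runs give 44% to 45%.

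**Power by analysis set.** The true correlation detectable with 80% power is, by Fisher's z, r = tanh[(1.96 + 0.84)/√(n − 3)].

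- EA arm only, n = 33: tanh(2.80/√30) = 0.47
- EA arm only, n = 26: tanh(2.80/√23) = 0.53
- Both arms, n = 66: tanh(2.80/√63) = 0.34
- Both arms, n = 52: tanh(2.80/√49) = 0.38

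Adjusting for three covariates (arm, baseline pressure, baseline brain value) replaces n − 3 by n − 6. This gives tanh(2.80/√60) = 0.35 and tanh(2.80/√46) = 0.39, so the adjustment costs about 0.01 in detectable correlation.

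**Why FDR does not help.** FDR controls for the number of tests, given P values that are valid one by one. Here each pooled P value for an affected region is already shifted by the shared arm effect. FDR changes the threshold, so the rates in the table are not those of the complete procedure, but the shift remains.

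**The case against.** The strongest reply is that pooling is nowhere stated. The wording fits a correlation inside the EA arm equally well, such a correlation holds its 5% error rate, and the analysis set of an exploratory imaging analysis is detail that an article may leave to a fuller document. The first two parts stand: a reader might infer that the arms will be pooled, but the text does not say so, and the inflation applies only if they are. The last part does not dispose of the point. The article does fix the test as a two-variable correlation, and each way of applying it has a cost that an arm-adjusted test on the same data avoids.

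Other replies also stand in part:
- A reader might conclude that the pooled test will report a link whenever treatment moves both measures. It will not. The error rate is inflated, and at the mild end (0.3 SD) it is only about 7%.
- A reader might suppose that regions will be chosen because they differ between EA and sham, which would favour large brain effects. No such rule is stated. The explicit group comparison in that section is patients against healthy controls.
- Multiple regression is already planned and could include arm. But its stated purpose is to find predictors of benefit, no arm term is named, and nothing says that it replaces the correlation test.
- The objective is preliminary, and a valid but weaker EA-only correlation is defensible for it. That limits the importance of the point but is no reason to prefer the weaker analysis.

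**Conclusion.** The point holds in conditional form. The named test has no arm term and its analysis set is open. If the arms are pooled and EA affects both measures, the chance of wrongly declaring a within-arm link rises from 5% to about 7% to 44% with 33 per arm, or about 7% to 37% with 26. These rates rest on the protocol's 0.8 SD pressure effect, an assumed brain effect of 0.3 to 1.5 SD, no within-arm correlation, and one test before FDR. If the EA arm alone is used, the error rate is sound. The detectable correlation then rises to about 0.47 (n = 33) or 0.53 (n = 26), from 0.34 (n = 66) or 0.38 (n = 52), and the comparison with sham is lost.

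A reader might infer that the trial's main result is in doubt. It is not: the primary comparison of systolic change and the sample size do not depend on this analysis. A reader might also infer that adjusting for arm would establish the mechanism. It would not. Brain change is not randomised, so even an adjusted association remains observational.

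**What to change.** In the Neuroimaging data analysis section, replace the two-variable correlation between brain change and systolic change with a partial correlation (Pearson or Spearman type), or a regression of systolic change on brain change. Use all randomised patients with usable scans, and adjust for arm, baseline systolic pressure and the baseline brain value. Report the correlation within each arm, or the arm-by-brain-change term, as a supplement to show whether the link differs between EA and sham. Keep the FDR correction on the resulting P values, and keep the analysis labelled exploratory.

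The cost is a few degrees of freedom and a sentence or two of text. No new data or visits are needed, and regression is already among the planned methods. The analysis set and the adjustment should be fixed before unblinding, so that neither can be chosen after the results are seen.
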